| 8. The quantity and timing of antibiotic and antiviral prescribing after Appointment Two and ≤28 days                                                                                   | Name, strength, frequency and quantity of antibiotics and antivirals prescribed after Appointment Two and ≤28 days                                                                                                                                                                                                                                                                                                                                                   | Retrospective collection from PCMR at least 2 months after recruitment |
| 9. Number of days on which antibiotics and antivirals are consumed ≤28 days                                                                                                             | Name of antibiotic and antiviral, and number of times per day the medicine was consumed                                                                                                                                                                                                                                                                                                                                                                              | Trial Diary  completed daily by participant               |

| Objective                                                                                                                       | Outcome Measure                                                                           | Source and published reference (where applicable)                  |
|---------------------------------------------------------------------------------------------------------------------------------|-------------------------------------------------------------------------------------------|--------------------------------------------------------------------|
| 10. Participant (or parent/carer if the participant is <16 years) intention to consult for similar future illnesses at 2 months | See Appendix 1 (Participant views questions 7 and 8)                                      | Questionnaire completed by participant 2 months post-randomisation |

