#### 2.1.2. SECONDARY CLINICAL OBJECTIVES

To investigate whether the use of a rapid POCT impacts on patient symptoms and antibiotic and antiviral consumption, as reported in the participant diary. The key secondary measure is derived from the symptom diary: the mean symptom score on days 2 to 4.

To investigate whether the use of a rapid POCT impacts on primary care presentations for RTI, antibiotic and antiviral prescriptions, and hospital admissions for RTI by review of the participants' primary care records.

To investigate whether the use of a rapid POCT impacts on patient beliefs and intentions, including participant confidence in the clinical management of the infection (reported on day 1) and participant intention to consult for similar illnesses in the future (reported at 2 months).

---

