| New or worsening symptoms                                                              | Binary     | Over days 2 to 28, the participant sees one or more symptoms increase to a score of $\geq 3$ , and is scored $\geq 3$ for at least one of the subsequent two days.                                                                                                                                                                           |
| Consumption of antibiotics                                                             | Count      | Number of days on which antibiotics are consumed on days 1 to 28.                                                                                                                                                                                                                                                                            |
| Counsumption of antivirals                                                             | Count      | Number of days on which antivirals are consumed on days 1 to 28.                                                                                                                                                                                                                                                                             |

**Participant views and study clinician views** were collected using the following eight questions at the indicated time points (P: participant, C: clinician). Given wording was for clinicians, with the same questions asked of participants but with wording adapted. The response options were as follows:

- 1 Strongly disagree
- 2 Disagree
- 3 Neither agree or disagree
- 4 Agree
- 5 Strongly agree

|     |                                                                                                                                | First contact | Appt 1 | End appt 1 | Allocation & test result | End appt 2 | 2 mths |
|-----|--------------------------------------------------------------------------------------------------------------------------------|---------------|--------|------------|--------------------------|------------|--------|
| [1] | I believe an antibiotic is needed to treat the patient's illness                                                               | P             | C      | P          | C                        | P          |        |

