#### 4.7. ANALYSIS OF THE SECONDARY OUTCOMES

The primary outcome analysis will be adapted to the secondary clinical outcomes by the choice of a suitable regression model. Effect sizes, 95% confidence intervals, and p-values will be presented (**Table 3** and **Table 4**, see Section 5).

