| Number (%) of patients consulting for RTI one or more times between appointment two and day 28   |    | XX (XX%)              | XX (XX%)         | XX.XX (XX.XX, XX.XX)                     | 0.XXX    |
| Number (%) of RTI consultations per patient between 29 days and 6 months                         | 0  | XX (XX%)              | XX (XX%)         | XX.XX (XX.XX, XX.XX)                     | 0.XXX    |
|                                                                                                  | 1  | XX (XX%)              | XX (XX%)         |                                          |          |
|                                                                                                  | 2+ | XX (XX%)              | XX (XX%)         |                                          |          |
| Number (%) of patients prescribed one or more antibiotics between appointment two and day 28     |    | XX (XX%)              | XX (XX%)         | XX.XX (XX.XX, XX.XX)                     | 0.XXX    |
| Number (%) of patients prescribed one or more antivirals between recruitment and appointment two |    | XX (XX%)              | XX (XX%)         | XX.XX (XX.XX, XX.XX)                     | 0.XXX    |
| Number (%) of patients prescribed one or more antivirals between appointment two and day 28      |    | XX (XX%)              | XX (XX%)         | XX.XX (XX.XX, XX.XX)                     | 0.XXX    |
| Number (%) of patients consuming any antibiotics from day 1 to 28 (participant report)           |    | XX (XX%)              | XX (XX%)         | XX.XX (XX.XX, XX.XX)                     | 0.XXX    |
| Number (%) of patients consuming any antivirals from day 1 to 28 (participant report)            |    | XX (XX%)              | XX (XX%)         | XX.XX (XX.XX, XX.XX)                     | 0.XXX    |

\*adjusting for participant age and chronic lung disease status

**Supplementary Table 1.** Recruitment by practice

|              | Intervention (n=XX) | Control (n=XX) |
|--------------|---------------------|----------------|
|              | n (%)               | n (%)          |
| Sites |                     |                |
| A            | XX (XX%)            | XX (XX%)       |
| B            | XX (XX%)            | XX (XX%)       |
| C            | XX (XX%)            | XX (XX%)       |
| D            | XX (XX%)            | XX (XX%)       |
| E            | XX (XX%)            | XX (XX%)       |

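### Antibiotic and antiviral consumption is defined as a number of days, but the SAP's only planned presentation is any versus none, with no row or named model for days consumed

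*Combined protocol and SAP*

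**What the plan says.** Protocol Table 1 words secondary objective 9 as "Number of days on which antibiotics and antivirals are consumed ≤28 days". Its outcome measure, taken from the daily Trial Diary, is "Name of antibiotic and antiviral, and number of times per day the medicine was consumed".

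SAP 2.10.2 carries this forward under the diary measures. Both rows are typed as counts: "Number of days on which antibiotics are consumed on days 1 to 28" for antibiotics and "Number of days on which antivirals are consumed on days 1 to 28" for antivirals.

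The analysis rule in SAP 4.7 is generic: "The primary outcome analysis will be adapted to the secondary clinical outcomes by the choice of a suitable regression model". It directs the results to Tables 3 and 4 of SAP Section 5. Table 3 (symptom measures) has no consumption row. Table 4 has two, each an n (%) per arm with an adjusted odds ratio: "Number (%) of patients consuming any antibiotics from day 1 to 28 (participant report" and "Number (%) of patients consuming any antivirals from day 1 to 28 (participant report".

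Two places word the objective more loosely, without a metric. SAP 2.1.2 speaks of "antibiotic and antiviral consumption, as reported in the participant diary", and the protocol's trial summary is similar but refers the reader to Table 1 for the full definition.

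**The concern.** The outcome is defined as one quantity and laid out for reporting as another, and the SAP does not explain the change. Any versus none cannot tell a full course from a shortened or stopped one.

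That distinction matters in this trial for two reasons found in the protocol.

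- **Course length is a plausible place for an effect.** The background (Section 1) reports that hospital studies of multiplex tests found shorter antibiotic courses, while only one found less prescribing overall. Section 1.1 counts short courses among the goals of stewardship.
- **Some participants will already be on treatment.** Protocol 5.4 (prior and concomitant therapies) admits patients already taking antibiotics or antivirals. Someone still taking a course on day 1 counts as a consumer in either arm, whatever the test shows. A count of days could still separate a course that is stopped from one that is continued.

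At stake is one non-key secondary outcome: whether it is reported as pre-specified or silently exchanged for another.

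**Working it through.** There is no stated figure to reproduce, because the documents give no sample size, power or expected value for consumption. The check has two parts.

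**1. Definition against shells**

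| Place | Measure | Form |
|---|---|---|
| Protocol Table 1, objective 9 | Days consumed, up to day 28 | Number of days |
| SAP 2.10.2, antibiotics | Days consumed, days 1 to 28 | Count |
| SAP 2.10.2, antivirals | Days consumed, days 1 to 28 | Count |
| SAP 4.7 | All secondary clinical outcomes | No model named |
| SAP Table 3 | No consumption row | None |
| SAP Table 4 | Any consumption, days 1 to 28 | n (%), odds ratio |
| SAP supplementary tables | No row for days consumed | None |

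The mismatch is the same for antibiotics and antivirals. No count model, rate ratio or difference in mean days is named for either. The protocol's tertiary mechanistic objective 2 uses any antibiotic consumption within 7 days. That is also binary, and the SAP places that analysis outside its scope, so it does not fill the gap.

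**2. Can any versus none stand in for days?**

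Formulas, with p the proportion taking any, d the mean days among takers and s their standard deviation:

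- Mean days per participant = p × d.
- Variance per participant = p(s² + d²) − (pd)².
- Odds ratio = [p₂/(1 − p₂)] / [p₁/(1 − p₁)], with arm 1 control and arm 2 POCT.
- Power for days = Φ(|difference|/SE − 1.96), with SE² = (variance₁ + variance₂)/206.

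Inputs: 206 per arm is the plan's expected diary yield for days 2 to 4 (80% of 514, divided by 2, is 205.6). Using it for days 1 to 28 is an assumption. All values of p and d, and s = 2 days, are also assumed and come from no document.

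| Assumed case (control v POCT) | Odds ratio | Mean days | Difference (control − POCT) | Power on days |
|---|---|---|---|---|
| (a) 50% v 50%; 7 v 5 days | 1.00 | 3.5 v 2.5 | 1.0 | about 86% |
| (b) 50% v 50%; 7 v 6 days | 1.00 | 3.5 v 3.0 | 0.5 | about 30% |
| (c) 60% v 45%; 5 v 7 days | 0.55 | 3.0 v 3.15 | −0.15 | about 7% |

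Case (a) in full: means are 0.5 × 7 = 3.5 and 0.5 × 5 = 2.5, and 1 − 2.5/3.5 = 29%. Variances are 0.5(4 + 49) − 12.25 = 14.25 and 0.5(4 + 25) − 6.25 = 8.25. SE = √(22.5/206) = 0.33, so 1.0/0.33 − 1.96 is about 1.07 and Φ is about 0.86.

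Case (c) runs the other way: the odds ratio is (0.45/0.55)/(0.60/0.40) = 0.55, with power of about 87% on any versus none, while mean days hardly differ. The two summaries answer different questions, and either can move without the other.

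**The case against.** **SAP 4.7 covers every secondary outcome.** A reader might infer that the objective will not be analysed at all. The documents do not support that. SAP 4.7 commits to analysing the secondary clinical outcomes with a suitable regression model, the count definition stands in 2.10.2, and Section 5 holds shells for the primary results paper only. What is missing is a row and a named model. This limits the point but does not remove it: the SAP says it exists partly so that others could run the analysis in the statistician's absence, and someone working from Table 4 would produce only odds ratios.

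**The objective is just consumption.** Under the looser wording in SAP 2.1.2 and the protocol summary, any versus none is a partial answer. The full definitions, however, specify days.

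**Any versus none is informative and more robust.** This stands in part. It separates delayed prescriptions never taken from those used, so it does not merely repeat the primary outcome, and another Table 4 row partly captures further prescribing up to day 28. It is also less exposed to the diary's stopping rule. Under protocol 6.9 and SAP 2.10.2, participants stop after two consecutive days with every symptom at zero, so recorded antibiotic-days are cut off by symptom duration, which may itself differ by arm. For example, someone on a 7-day course from day 1 whose diary stops after day 5 is recorded as 5 days. That is a reason for a stated handling rule and for keeping the binary rows, not for exchanging the outcome without comment.

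**Consultations look like the same fault.** SAP 2.10.2 types RTI consultations as a count for both periods, while Table 4 shows the 28-day period as one or more, so a reader might infer a second substituted outcome. It is not one: protocol objective 6 is a proportion, and the Table 4 row matches it. Only the SAP label is out of line.

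**Conclusion.** The inconsistency is real and rests on the text alone. Days consumed is the pre-specified outcome in both documents, the only planned presentation is any versus none, and no reason is given. If the shells are followed as drawn, a different outcome replaces it, and that outcome cannot show shorter or stopped courses.

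Its size in this trial cannot be derived from the documents. The 29% reduction alongside an odds ratio of 1.00 depends on the assumed 50%, 7 days and 5 days. It shows that the measures can diverge, not that they will, and should not be read as a forecast.

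This is a minor point. It concerns a non-key secondary outcome and leaves the primary and key secondary inferences untouched.

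**What to change.** 1. Add two rows, antibiotic-days and antiviral-days over days 1 to 28. Report the mean (SD) and n per arm, and the difference in means adjusted for age group and chronic lung disease, with the bias-corrected and accelerated bootstrap interval that Table 3 already uses for durations. This copes with the many zeros expected.
2. State how two kinds of unrecorded day are treated: days after the diary stops at symptom resolution, and days missing before that. The existing rule in SAP 2.10.2 covers symptom ratings only. Add a sensitivity analysis under a different assumption about post-resolution days, because the truncation may differ by arm.
3. Keep the any-versus-none rows as supportive.
4. State in SAP 2.10.2 that the diary also records antivirals. Its description of daily medication recording mentions antibiotics only.
5. Align the count label for 28-day RTI consultations with protocol objective 6. No new consultation row is needed.

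If the team prefers any versus none as the outcome, the alternative is to redefine it as binary in SAP 2.10.2 and justify the departure from the protocol.

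The cost is two table rows, a short handling rule and one sensitivity analysis, using diary data already planned for collection. The remaining downside is that some end-of-course days go unrecorded, so the day counts will be somewhat too low and should be described as such.

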| Confidence to manage patient without antibiotics (self-efficacy)              | 4. The point-of-care test would help in making the right decision about whether the patient needs antibiotics [Step 2]
5. The point-of-care test would have helped B /has helped C in making the right decision about whether the patient needs antibiotics [Step 5]                                                                                                                                             | Strongly disagree; Disagree; Neither agree nor disagree; Agree; Strongly agree |

|                                                                          |                                                                                                                                                                                                             |                                                                                      |
|--------------------------------------------------------------------------|-------------------------------------------------------------------------------------------------------------------------------------------------------------------------------------------------------------|--------------------------------------------------------------------------------------|
|                                                                          | 6. I am confident that the patient will believe they are getting the right treatment [Steps 2 and 5]                                                                                                        |                                                                                      |
| Confidence to manage similar infection without antibiotics in the future | 7. If a patient has a similar infection in future I am likely to prescribe them antibiotics [Step 5]
8. If a patient has a similar illness in future I would like to use the POCT RM [Step 5] | Strongly disagree; Disagree;
Neither agree nor disagree;
Agree; Strongly agree |

ANot presented in order collected

BWording for control group

CWording for intervention group

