Clinician and participant views, pre-randomisation, will be tabulated by allocated group for the full analysis set (**Supplementary Table 3a, 3b; Supplementary Table 4a**, see Section 5). Clinician views, post-randomisation, will be tabulated by allocated group for the per protocol set, and the null hypothesis of no difference in the population in views between the two groups will be tested using an ordered logistic regression model (**Supplementary Table 4b**, see Section 5). Participant views, post-randomisation, will be tabulated by allocated group for the full analysis set, and the null hypothesis of no difference in the population in views between the two groups will be tested using an ordered logistic regression model (**Supplementary Table 3c, 3d**, see Section 5).

The result of the POCTRM test for each participant in the intervention group will be presented, with the probability of a prescription of antibiotic or of a antiviral for each observed result (**Supplementary Table 5**, see Section 5).

The change in response to the question “I believe an antibiotic is needed to treat the patient’s illness” for clinicians in the per protocol set is tabulated for the three groups, POCTRM virus detected, POCTRM no virus detected, no POCTRM group (**Supplementary Table 6**, see Section 5).

The aim of the primary results paper is to present information on the nature and magnitude of the effect of the POCTRM on clinical outcomes, and upon potential mechanisms for that impact on outcomes. These results will guide the scope and approach to a causal analysis of potential mechanisms for any clinical benefit of POCTRM, to be reported in a separate paper.

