|                                                                                                                         | Disagree                   | XX (XX%)              | XX (XX%)         |                      |
|                                                                                                                         | Strongly disagree          | XX (XX%)              | XX (XX%)         |                      |
| The point of care test would have / has helped in making the right decision about whether the patient needs antibiotics | Strongly agree             | XX (XX%)              | XX (XX%)         | 0.XXX                |
|                                                                                                                         | Agree                      | XX (XX%)              | XX (XX%)         |                      |
|                                                                                                                         | Neither agree nor disagree | XX (XX%)              | XX (XX%)         |                      |
|                                                                                                                         | Disagree                   | XX (XX%)              | XX (XX%)         |                      |
|                                                                                                                         | Strongly disagree          | XX (XX%)              | XX (XX%)         |                      |
| I am confident that the patient will believe they are getting the right treatment                                       | Strongly agree             | XX (XX%)              | XX (XX%)         | 0.XXX                |
|                                                                                                                         | Agree                      | XX (XX%)              | XX (XX%)         |                      |
|                                                                                                                         | Neither agree nor disagree | XX (XX%)              | XX (XX%)         |                      |
|                                                                                                                         | Disagree                   | XX (XX%)              | XX (XX%)         |                      |

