aOrdinal logistic regression model, adjusting for baseline participants' views, age and chronic lung disease status

**Supplementary Table 5.** POCTRM result for participants allocated to the intervention group, with subsequent prescription of antibiotics and antivirals.

|                                 | Number of cases
(N=)                              | Number prescribed
antibiotic at
appointment 2             | Number prescribed
antiviral at
appointment 2              |
|---------------------------------|------------------------------------------------------|-----------------------------------------------------------------|-----------------------------------------------------------------|
|                                 | n (% of participants
in POCT RM group) | n (% of participants
with this POCT RM
result) | N (% of participants
with this POCT RM
result) |
| No valid result                 | XX (XX%)                                             | XX (XX%)                                                        | XX (XX%)                                                        |
| No microbe detected             | XX (XX%)                                             | XX (XX%)                                                        | XX (XX%)                                                        |
| Single microbe detected  |                                                      |                                                                 |                                                                 |
| Bordetella pertussis            | XX (XX%)                                             | XX (XX%)                                                        | XX (XX%)                                                        |
| Bordetella parapertussis        | XX (XX%)                                             | XX (XX%)                                                        | XX (XX%)                                                        |
| Chlamydia pneumoniae            | XX (XX%)                                             | XX (XX%)                                                        | XX (XX%)                                                        |

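### Clinician views item 5 is worded differently in each arm but tested between arms with one p-value, which cannot be read as an effect on confidence in the POCT

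*Combined protocol and SAP*

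**What the plan says.** Protocol Appendix 1 lists clinician item 5, asked at Step 5 after allocation, as "The point-of-care test would have helped B /has helped C in making the right decision". Its footnote B reads "Wording for control group" and its footnote C reads "Wording for intervention group". SAP section 2.10.2 repeats the split wording in its list of views questions.

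SAP section 4.8 states that "Clinician views, post-randomisation, will be tabulated by allocated group for the per protocol set", and that "the null hypothesis of no difference in the population in views between the two groups will be tested using an ordered logistic regression model". The results go to Supplementary Table 4b. There item 5 appears as the single row "The point of care test would have / has helped in making the right decision about whether the patient needs antibiotics", with its own p-value cell like every other item. The table footnote describes the model: "Ordinal logistic regression model, adjusting for baseline participants' views, age and chronic lung disease status".

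The item bears on the secondary mechanistic objective (Protocol Table 3, SAP section 2.1.4), part of which is to describe the effect of POCT results on confidence in the test as a guide to prescribing. Neither document exempts item 5 from testing, adds a caveat, or explains how the two wordings are made comparable.

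**The concern.** A between-arm test of a views item is informative when both arms answer the same question, because allocation is then the only systematic difference. Here the question changes with allocation. A control clinician judges a hypothetical test; an intervention clinician judges a specific result already seen.

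Of the items in Supplementary Table 4b, item 5 is the one that asks directly about the value of the test for the decision in hand, so its p-value is the one most likely to be taken as the answer to the confidence part of the objective. A small p-value could be reported as the POCT raising or lowering clinician confidence when it reflects only the change from a hypothetical to an experienced question. A large one could hide a real change that the wording offsets.

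**Working it through.** The documents state no figure for item 5, so the check is mainly one of design.

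**1. What is observed.** Write Y(arm, wording) for the answer.
- Control clinicians supply Y(control, hypothetical).
- Intervention clinicians supply Y(intervention, experienced).
- Nobody supplies the other two combinations, and Y(control, experienced) cannot be asked, because control clinicians have no practice result to judge.

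**2. What the model estimates.** On the cumulative log-odds scale, the arm coefficient is

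coefficient = (effect of allocation with wording held fixed) + (effect of wording within an arm).

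There is one contrast and two unknowns, so only the sum is identified. A coefficient of zero is not the null of no effect on confidence, and a non-zero coefficient is not evidence of one.

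**3. Whether anything in the plan separates the two.** Randomisation balances patients, not questions. The listed covariates are baseline views, age and chronic lung disease. None varies the wording within an arm, so none can help.

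**4. How far the problem reaches.** In Appendix 1 the arm-specific footnotes B and C are attached, among the clinician items, only to item 5. Items 1, 2, 3, 6, 7 and 8 have one wording for both arms, and this point does not touch their tests.

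**5. Illustration of size (assumed inputs).** Take 244 per arm from the sample size section. That figure reproduces for 60% versus 45% at 90% power with the continuity-corrected two-proportion formula (231 without correction), and 488/0.95 rounds up to the target of 514. The size of the per protocol set is not stated, so 244 is a stand-in.

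Suppose confidence is truly equal in both arms and wording alone shifts the five-category answers by a cumulative odds ratio OR. The proportional-odds information is I = (N/12)(1 − Σp̄³), where p̄ is the average of the two arms' category probabilities. The chance of p<0.05 is approximately Φ(ln OR·√I − 1.96).

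Worked case: one arm 5/15/30/35/15% and OR 1.5 give the other arm 3.4/10.9/25.7/39.1/20.9%, that is, 50% against 60% agreeing or strongly agreeing.
- Σp̄³ = 0.0805
- I = (488/12)(0.9195) = 37.4
- ln(1.5)·√37.4 = 0.405 × 6.115 = 2.48
- Φ(2.48 − 1.96) = 0.70

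Across three assumed distributions (5/15/30/35/15, 20% in each category, 2/5/18/50/25):

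| Wording-only OR | Chance of p<0.05 |
|---|---|
| 1.0 | 5% |
| 1.25 | 26–29% |
| 1.5 | 67–72% |
| 1.75 | 91–94% |
| 2.0 | 98–99% |

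A rank-test simulation (3,000 runs, first distribution) gave 4.9%, 68% and 99% at OR 1.0, 1.5 and 2.0.

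**The case against.** The case for leaving the row as it is has several parts.

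The SAP claims only to test for a difference in views. It does not call the result an effect on confidence, and Supplementary Table 4b prints percentages and a p-value without an effect size. The row shows both wordings, and the table title says that intervention clinicians had learned the result, so an attentive reader can see the difference. The split can hardly be avoided, because control clinicians cannot be asked whether a test they did not have helped. Anticipated against experienced usefulness may itself be of interest. The objective is to describe, item 8 offers a like-for-like comparison in the same table, and SAP section 4.8 defers a fuller causal analysis of mechanisms to a separate paper.

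Most of this stands. The test is valid for equality of two answer distributions, and it would be too strong to call it invalid. What it does not answer is that the plan puts item 5 under the same null, in the same format and without comment, as items for which that null does bear on the effect of allocation. Showing both wordings tells the reader that they differ, but not that the p-value lacks the meaning it has in the other rows.

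Two stronger readings are tempting and are not supported.
- **Participants.** Supplementary Table 3c has no row for participant item 5, which has the same split wording. A reader might infer that the SAP recognised the problem for participants and missed it for clinicians. But SAP section 4.8 tests post-randomisation participant views with no exemption for item 5. The schedule in section 2.10.2 marks participants at the end of Appointment Two for item 5 and not item 6, whereas Table 3c shows item 6 and not item 5. That is a mismatch between schedule and table shell, and says nothing about intent.
- **Comparison by test result.** A reader might infer that comparing item 5 between virus detected and not detected within the intervention arm answers the objective. That comparison is not randomised. Detection may go with type and severity of illness, and adjusting for the clinician's own item 4 does not remove this. For prescribing, SAP section 4.8 uses the control arm's laboratory result to separate such influences.

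**Conclusion.** The point holds in a limited form. For clinician item 5, wording and allocation cannot be separated, so the planned p-value cannot be read as an effect of the POCT on confidence in the test. This follows from the text of Appendix 1 and Supplementary Table 4b and needs no numerical assumption.

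The illustrative rejection rates do rest on assumptions: the response distributions, the wording shift, 244 independent answers per arm, and no true difference in confidence. They show that a moderate shift would often reach significance. They do not show that such a shift exists, and a reader should not infer one.

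The consequence is confined to one row of a supplementary table for a secondary mechanistic objective. The primary outcome, the key secondary outcome, the sample size, the primary mechanistic item (clinician item 1) and the other rows of the table are unaffected.

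**What to change.** - In Supplementary Table 4b, remove the between-arm p-value for item 5. Show the control and intervention wordings as two separate rows, labelled not comparable, and add the matching exception to SAP section 4.8.
- For the between-arm comparison on the related construct, rely on item 8 (wish to use the test in a similar future illness), which has common wording and is already tested in that table. Align the item numbering at the same time: Appendix 1 and SAP section 2.10.2 place item 8 at Step 5, but Protocol section 6.6.3 and Table 3 stop at question 7.
- If participant item 5 is reported, treat it in the same way.
- Optionally, within the intervention arm, present item 5 by virus detected versus not detected, adjusted for the clinician's item 4 at Appointment One (asked before randomisation in one wording), and label it descriptive and non-randomised.

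The cost is an edit to one table shell and a sentence in the SAP, plus one simple model if the optional analysis is wanted. The plan already collects all the data. What is given up is a p-value that could not be interpreted against the objective.
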